### Pilot Study of the Leduin Program

In a pilot study, we assessed the feasibility, acceptance, and engagement of the leduin program, implementing it with 101 students of 9th and 10th-grade in high schools and secondary schools in North Rhine-Westphalia and Lower Saxony, Germany, from November 2022 to February 2023 ([name] and [name], unpublished data, 2024). A total of 13 interviews with participating adolescents aged 14 to 17 years and 6 interviews with their teachers were conducted to evaluate acceptance and initial effectiveness. These qualitative findings indicate that the social media–based prevention program was successfully conducted, well-received by participants, and executed with high commitment. Participants reported positive subjective learning outcomes in social media use, self-care, and stress reduction and perceived the leduin program as personally beneficial and enriching. Although the program yielded favorable results, its accessibility presented a substantial hurdle in the recruitment phase. We conducted informational sessions in schools and a youth center to educate adolescents about the program, enabling them to make informed choices about participating in their leisure time. However, the participation rates varied significantly among schools, with certain classes showing high engagement, while others had minimal involvement. This variation underscores the importance of developing effective strategies to engage adolescents in social media–based prevention programs. Consequently, in the fifth step of the intervention mapping approach as the subject of this study, our focus is to examine and enhance accessibility to guarantee effective program execution.

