### Reach

The focal point of our study is to encompass a broad and representative demographic of 9th- and 10th-grade adolescents. To achieve this, we are targeting a diverse population from various school types, including grammar schools, comprehensive schools, secondary schools, and independent schools. Moreover, recognizing the importance of reaching adolescents undergoing high stress, recruitment efforts are also extended to youth centers and therapeutic facilities. We will explore the characteristics of adolescents who have consented to participate. Based on insights from the pilot study, we anticipate varying levels of engagement among the participants: some may actively engage with the program’s social media content, while others may have minimal to no interaction although initially interested. This variance allows for a quasi-experimental design, using engagement levels (ranging from none to high) as the basis for group assignment. Such a design is capable of highlighting differences between these engagement groups, and we will explore the predictors that are associated with active engagement or no or low engagement. We will also conduct a qualitative process evaluation to explore the facilitators and barriers encountered during recruitment. This will involve the recruitment team documenting feedback about the program and information event, as well as the reasons participants choose to join or decline participation. This documentation will be captured both in written form and verbally.

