### Effectiveness

The program’s effectiveness will be evaluated by its impact on life skills, social media–related skills, health status, risk behaviors, and school performance. Using the quasi-experimental design, we aim to test the hypothesis that enhancing digital life skills through the intervention leads to improved social media skills and reduced risk behaviors. To detect medium-sized effects, a power analysis indicates the need for 128 adolescent participants (power=0.8, α=.05), aligning with existing evidence of medium effect sizes in digital interventions (d=0.30 to 0.76) [72]. This evaluation will provide crucial data for potential effectiveness, shaping the direction of future trials.

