### Recruitment

This accessibility study will recruit participants via schools, youth centers, and therapeutic facilities across Germany. Adolescents from various school types (grammar, secondary, comprehensive, and independent) and socioeconomic backgrounds are targeted. Recruitment spans several federal states (Berlin, Mecklenburg-Western Pomerania, North Rhine-Westphalia, Saxony, Lower Saxony, and Thuringia), chosen for representativeness and synchronized holidays, encompassing both rural and urban areas. State school participation requires ethical approval and ministry or school board consent. Schools, youth centers, and therapeutic facilities are randomly selected within these states.

Recruitment will begin once approvals are obtained, with invitations issued in waves based on response rates. Teachers, youth workers, and therapists initially agreed to participate (Multimedia Appendix 1). Adolescents are then recruited through digital information events, which aim to build motivation to participate through highlighting the relevance of the programs’ content for their life stage (Multimedia Appendix 2). In addition to research findings on that, key adolescent concerns were identified in the pilot study. The use of Instagram minimizes participation effort and the recruitment in schools fosters group dynamics. Further, the program incentivizes engagement with rewards and ensures anonymity and confidentiality, creating a safe space for discussing sensible and at the same time interesting topics. Finally, together with their parents, adolescents agree to participate in the study.

To join the study, participants need an Instagram account, must be proficient in German, and must be aged 14-17 years. The recruitment goal includes 2 classes from grammar schools, 3 classes from secondary schools, and 1 class from an independent school per state, plus 20 adolescents from youth centers and therapeutic institutions in each state, accommodating additional participants if interested.

As we are taking an innovative approach, it is not clear how complete the recruitment will be. The sample size depends on adolescents who voluntarily want to participate. Since adolescents work on the program in their free time, it can be assumed that fewer will participate than in compulsory programs conducted in school. Recruitment will start in May 2023 and end as soon as the target criteria are met or the program starts in September.

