### Data Analysis

#### Statistical Methods

Quantitative analyses will vary according to the different dimensions of the RE-AIM framework [71]. The software R Studio (Posit) and SPSS (IBM Corp) will be used [95]. Multilevel logistic regressions will be conducted to evaluate the dimensions of reach, acceptance, and implementation. Here, the extent to which the following variables influence institutions’ initial interest in the program, individuals’ initial willingness to participate in the program, completeness of data, and individual engagement within the program is examined: socioeconomic status, gender, age, mode of recruitment (school, youth center, and therapeutic facility), school type, performance, well-being, life satisfaction, and mental health. The initial interest of institutions in the program is operationalized by the proportion of institutions (schools, youth centers, and therapeutic institutions) that participated in an information session. The initial willingness of individuals to participate in the program is assessed by the percentage of students who decide to participate in the program after an information session. The completeness of data is examined by the percentage of data in the preintervention, postintervention, and follow-up surveys, and individual engagement is measured by the participants’ self-assessment.

For quantitative analyses of the dimensions of reach, effectiveness, and sustainability, mixed-effect multilevel regression analysis with institutions (school, youth center, and therapeutic facility), classes, and individuals as evaluation levels and 3 measurement points (preintervention, postintervention, and follow-up) will be carried out. The multilevel structure will be assumed if the actual design effect resulting from the intraclass correlation is >2 [96]. The influence of covariants such as gender, age, and socioeconomic status will be controlled. In addition, the individual courses in the outcome variables, as described before, will be examined by using latent growth models across the 3 time points. Logistic regressions will be conducted to investigate the impact of the program on participants’ addictive or disordered social media use by comparing pre- and postintervention data.

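### Class and institution levels stay in the mixed-effect regressions only if the estimated design effect exceeds 2, so tests of effects that vary between clusters are anti-conservative

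*Protocol article*

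**What the plan says.** In the protocol article, the second paragraph under Statistical Methods plans, for reach, effectiveness and sustainability, a "mixed-effect multilevel regression analysis with institutions (school, youth center, and therapeutic facility), classes, and individuals as evaluation levels and 3 measurement points". The next sentence makes this conditional: "The multilevel structure will be assumed if the actual design effect resulting from the intraclass correlation is >2". The article does not say what replaces the multilevel model when the condition fails. It mentions neither cluster-robust standard errors nor fixed cluster effects.

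Other parts of the article bear on the rule:

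- Recruitment is by intact group. The goal is "2 classes from grammar schools, 3 classes from secondary schools, and 1 class from an independent school per state" in six states, plus 20 adolescents per state from youth centers and therapeutic institutions (Recruitment).
- The comparison for effectiveness is between engagement groups, "using engagement levels (ranging from none to high) as the basis for group assignment" (Reach). The pilot reported "certain classes showing high engagement, while others had minimal involvement" (Pilot Study of the Leduin Program).
- Table 3 lists the mixed-effect model for effectiveness and maintenance without repeating the condition.
- The multilevel logistic regressions for reach, acceptance and implementation are described in the preceding paragraph, with no design-effect condition.

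**The concern.** A design effect of 2 means that clustering has doubled the variance of a between-cluster estimate. A rule that tolerates anything up to that point accepts standard errors that are too small by a factor of up to √2 = 1.41 for a predictor constant within clusters. Predictors that are partly clustered are affected less.

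Engagement group is the central exposure in the effectiveness analysis, and the pilot suggests that it clusters by class. If outcomes cluster too, the engagement-group contrasts inherit part of this error. Their intervals would be too narrow and their p-values too small.

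The decision also rests on an estimate from the same data. With the many outcomes in Table 2, some could be analysed with the cluster levels and others without, partly by chance. The article intends these results to inform the direction of later trials, so spurious engagement effects would have consequences.

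**Working it through.** **Inputs.** The threshold (design effect >2) and the levels come from Statistical Methods. The target of 6 classes × 6 states = 36 classes comes from Recruitment, and the 283 participants from Results. The article gives no intraclass correlation (ICC) or achieved cluster size, so those below are assumptions. Tests are taken as two-sided at 5%.

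**Step 1: the plan's own sample size.** Under Effectiveness the article states "a power analysis indicates the need for 128 adolescent participants (power=0.8, α=.05". Its cited range for d runs from 0.30 to 0.76. A two-sample t-test with d = 0.5, equal groups, two-sided α = 0.05 and power 0.80 needs 63.77, so 64 per group and 128 in total. The figure is reproduced with independent observations and contains no allowance for clustering. The rule is therefore not offset elsewhere.

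**Step 2: a test that always ignores clustering.** With design effect DE = 1 + (m − 1) × ICC and a predictor constant within clusters, the true error is 2 × [1 − Φ(1.96/√DE)].

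| DE | 1.96/√DE | True error |
|---|---|---|
| 1.25 | 1.753 | 8.0% |
| 1.5 | 1.600 | 11.0% |
| 1.75 | 1.482 | 13.8% |
| 2.0 | 1.386 | 16.6% |

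For a predictor that is itself only partly clustered, the relevant quantity is about 1 + (m − 1) × ICC_x × ICC_y. At the threshold (m − 1) × ICC_y = 1, so ICC_x = 0.5 gives 1.5 and hence about 11%. A simulation with 36 classes of 8 and ICC 0.14 (DE = 1 + 7 × 0.14 = 1.98) gave 15.3%, 10.1%, 8.4% and 4.4% for predictor ICCs of 1, 0.5, 0.3 and 0.

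**Step 3: the two-step rule as written.** The design effect was estimated in each simulated data set, and the clustered analysis was used only if the estimate exceeded 2. Results for a cluster-level predictor, 6,000 data sets each:

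| Clusters × size | True DE | Ignoring clustering | Two-step rule | Always modelled | Estimate ≤2 |
|---|---|---|---|---|---|
| 36 × 8 | 1.5 | 10.4% | 9.6% | 4.8% | 94% |
| 36 × 8 | 2.0 | 16.8% | 9.1% | 4.9% | 52% |
| 16 × 8 | 1.5 | 11.0% | 8.8% | 4.8% | 86% |
| 16 × 8 | 2.0 | 17.3% | 8.8% | 4.8% | 54% |

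The two-step error is below the naive error because data sets with a large between-class spread tend to trigger the correction. A separate run at 36 × 8 gave 8.8%, 10.7%, 9.9% and 6.3% at true design effects of 1.35, 1.7, 2.0 and 2.4, so the peak lies below the threshold. Over 15 to 36 classes of 4 to 8, the range is about 8 to 13% for a cluster-level predictor and about 6 to 8% for one with half its variance between classes. Always modelling the clustering gives roughly 5% with 8 per class.

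**Step 4: the ICC that the rule tolerates.** DE = 2 at ICC = 1/(m − 1).

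| m per class | Trigger ICC |
|---|---|
| 128/36 = 3.56 | 0.39 |
| 5 | 0.25 |
| 283/36 = 7.86 | 0.146 |
| 10 | 0.11 |
| 20 | 0.053 |

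The two divisions by 36 assume that every participant comes from the target classes, which the article does not say.

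**Step 5: contrasts that are not affected.** With three time points, a class effect shared across times cancels from the pre-post change. In simulation with class ICC 0.143 and person variance 0.30 or 0.45, dropping only the class level gave errors of 5.6% and 5.0%. This assumes no class-by-time variance.

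**The case against.** The rule carries a citation, and the effectiveness analysis is presented as giving first insights before a cluster-randomized trial, so no confirmatory decision rests on it. That limits the severity, but the rule still only removes a protection that the preceding sentence plans.

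Several stronger readings are tempting, and the documents do not support them.

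- *The true type I error reaches 16 to 17%.* That is the error of a test that always ignores clustering at a design effect of 2. The protocol switches on the estimated value, and the two-step procedure has a lower error.
- *The analyses of who is reached and who engages are invalid.* School type and mode of recruitment are named as predictors in the multilevel logistic regressions, which are stated without the condition. The mixed-effect paragraph does mention reach, but Table 3 uses that model only for effectiveness and maintenance.
- *Repeated measurements will be treated as independent.* On a literal reading the individual level might also be dropped, since 1 + 2 × ICC exceeds 2 only when the within-person correlation is above 0.5. The reading is strained: the same paragraph specifies three measurement points and adds latent growth models, and the rule reads naturally as being about class and institution. Dropping the person level as well would make pre-post tests conservative (1.0% and 0.3% in the simulations of Step 5).
- *The levels will almost always be dropped.* This depends on cluster sizes and ICCs that are not given. The 36 classes are a goal, and fewer, larger classes would lower the trigger. The pilot observation concerns participation and engagement; it does not give the ICC of the outcomes.

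**Conclusion.** The point holds within a limited scope and should be fixed. As written, the rule makes inference anti-conservative in the mixed-effect regressions for effects that vary between clusters, and for engagement-group contrasts to the extent that engagement clusters by class. The nominal 5% becomes about 8 to 13% for a cluster-level predictor and about 6 to 8% for a predictor with half its variance between classes.

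These figures assume two-sided tests and 15 to 36 classes of 4 to 8, with true design effects at or somewhat below the threshold. The 11.0% and 16.6% figures describe a test that never corrects and should be quoted only as such. Purely within-class contrasts are about nominal, and so is pre-post change when classes do not differ in change. A claim that all p-values in the study are too small would go beyond what the article supports.

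**What to change.** Delete the design-effect threshold. State that every mixed-effect regression keeps random intercepts for class and institution, together with the individual level for the repeated measurements, whatever the estimated ICC. If a variance component is estimated as zero, leave it at zero. If a level cannot be estimated, use cluster-robust standard errors with a small-sample correction. Report the ICCs for each outcome descriptively; they will also help to plan the cluster-randomized trial.

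This changes one sentence and needs no new data. The cost is slightly wider intervals and an occasional singular fit.

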#### Monitoring

Since the leduin study is not a clinical study, it is not expected that the participants will experience any harm. Therefore, the use of a data monitoring committee is waived. However, communication within the program will be monitored by an internal monitoring team in accordance with netiquette [98]. Violations of netiquette will be commented on and discussed within the program, and if necessary, the authors will be excluded from the program if there is no improvement. If harm is unexpectedly caused to a participant during the program, the program will be interrupted if there are indications that the harm may have been caused by the program. After review, the program will either be revised or continued.

### Ethical Considerations

The leduin study has been positively assessed by the ethics committee of the Greifswald University Medical School (BB 190/22). Approval for the study has also been sought from the relevant education authorities and ministries for state schools in Germany. The data protection regulations have been developed with the data protection officer of the University of Greifswald and a register of processing activities is available. If important protocol modifications are made, this will be communicated to the responsible ethics committee, the school authorities and ministries, the data protection officer, and the study participants.

Participating adolescents and their parents consent to their participation in the study. Consent is given on the basis of the study information and information events.

### Dissemination Policy

Trial results will be communicated to participants, schools, prevention professionals, and authorities via publication and in edited form in a brochure and on the project website, further through publications, conference contributions at academic conferences, and practitioners’ congresses (eg, Digitallabor and Medienschule).

## Results

Recruitment for the study was planned from May 2023 until the beginning of the leduin program in October 2023. As of March 2024, a total of 283 participants agreed to participate in the study.

## Discussion

### Overview

Social media offers effective ways of reaching a broad audience and can be used to address risk behavior and skill development [3,15,22]. To this aim, life skills can be a holistic approach. Despite the prevalence of digital training, few are evidence-based and access to the target audience remains challenging [27,29,30,33]. Moreover, existing life skills training often fails to address digital challenges. Further, the potential of using existing social media to reach adolescents has not been exploited. Our program is designed to improve digital life skills using Instagram, a platform that aligns with adolescents’ habits and offers interactive features suitable for e-learning. The program addresses both the benefits and the risks associated with social media use. Our upcoming study aims to assess the accessibility of this innovative approach, leveraging existing social media to develop digital life skills, with future plans to evaluate its effectiveness.

In a pilot study, the leduin program was tested with 101 students in 9th and 10th grade across schools in North Rhine-Westphalia and Lower Saxony, Germany ([name] and [name], unpublished data, 2024). The study, conducted from November 2022 to February 2023, involved interviews with 14- to 17-year-old participants and their teachers to evaluate the program’s acceptance and initial effectiveness. Results showed positive reception and commitment, with participants reporting beneficial learning outcomes in social media use, self-care, and stress reduction. However, our pilot study highlighted substantial challenges in reaching the target group. While some classes were very interested in participating, others showed minimal involvement. This disparity suggests that simply making the program available is not sufficient. Effective strategies are needed to actively engage adolescents, ensuring they are both aware of and interested in participating. The leduin program is crafted to subtly enhance life skills through everyday activities with minimal effort over an extended period with spaced learning, aligning with effective learning and skill acquisition theories [69,70]. While social media proves effective in health interventions [22,30], participation depends on the individual’s choice. Accordingly, adolescents might not fully appreciate the personal benefits of such engagement in their developmental stage [9]. To address this, we aim to reach adolescents through institutions already engaged in preventative work. However, since the intervention occurs during leisure time, even with its low barriers, consistent participation cannot be assured. Additionally, there is a possibility of waning intrinsic motivation over time.

The objectives of the accessibility study focus on identifying effective methods to engage adolescents in a digital life skills program on social media. It aims to encourage participation and sustain engagement to improve digital life skills. The study uses the RE-AIM model to guide its design, primarily focusing on the dimension “reach”. Accordingly, key aspects include reaching a representative adolescent sample, examining the characteristics of consenting participants, and analyzing the variance in engagement levels. We thus aim to assess the accessibility of a social media intervention amidst heightened stress levels in schools and among adolescents post–COVID-19 pandemic, as indicated by our pilot study. Despite the critical need for prevention work, overall accessibility may be significantly constrained due to resource limitations, independent of the program’s specifics.

The study further aims to identify relevant aspects of the other dimensions of the RE-AIM framework (effectiveness, acceptance, implementation, and maintenance) and thus examines the program’s effects on life skills and social media–related skills, along with health, risk behavior, and school performance. It assesses program acceptance among schools, youth centers, and therapeutic facilities; the effectiveness of data collection, participant interaction, and retention rates on Instagram; and the long-term impact of the intervention. While this approach may yield valuable information, further studies must follow to fully evaluate the aspects of the comprehensive RE-AIM model.

